**SYNOPSIS**

| Title | **A Phase III, randomized, non-inferiority trial, to assess the efficacy and safety of Dihydroartemisinin+Piperaquine (DHA+PPQ, Artekin) in comparison with Artemether+Lumefantrine (A+L, Coartem) in children with uncomplicated *P*. *falciparum* malaria.** |
| --- | --- |
| Protocol Number | ST3073-ST3074 DM040011 |
| Phase | III |
| Methodology | A phase III, randomized, open label, two arms study. |
| Study Duration | Each patient will be followed for 42 days. |
| Country | 5 countries: Mozambique, Kenya, Burkina Faso, Uganda, Zambia. |
| Study Center(s) | 5 sites (one site in each country). |
| Objectives | Primary objective:  The primary objective of the study is to measure the Day 28, PCR corrected cure rates of Artekin and Coartem and demonstrate that the cure rate of Artekin is non-inferior to that of Coartem (non-inferiority margin = 5%). This cure rate is defined as the proportion of patients with adequate clinical and parasitological response at Day 28 plus those treatment failures identified as new infection by PCR.  In order to compare the study results with the historical ones, the criteria described in the WHO document (“Assessment and Monitoring of Antimalarial Drug Efficacy for the Treatment of Uncomplicated Falciparum Malaria – 2003”. See chapter 7, section 7.3) will be used.  .  Secondary objectives:  - Comparison of the uncorrected Day 28 cure rates of both drugs.  - Comparison of the safety profiles of the two treatments.  - Comparison of times of parasite clearance.  - Comparison of time of fever clearance.  - Comparison of gametocytes (prevalences and densities).  - Comparison of haemoglobin (Hb) changes from day 0 to day 28 and to day 42.  - Comparison of cure rates at D42 (PCR corrected and uncorrected). |
| Number of Subjects | 1500 patients of which 500 are expected to be recruited in Mozambique (1000 DHA+PPQ; 500 A+L) in the modified ITT population (see section 9.1).  . |
| Diagnosis and Main Inclusion Criteria | Males and Females aged between 6 months and 59 months inclusive, body weight at least 5 Kg, microscopically confirmed, monoinfection of *Plasmodium falciparum*, history of fever or presence of fever (axillary temperature at ≥ 37.5 °C), written informed consent. |
| Study Product, Dose, Route, Regimen | Dihydroartemisinin+Piperaquine (DHA+PPQ, Artekin™).  Tablets containing 20 mg or 40 mg of Dihydroartemisinin and 160 mg or 320 mg of Piperaquine. |
| Duration of administration | Three days |
| Reference therapy | Artemether+Lumefantrine (A+L, Coartem).  Tablets containing 20 mg of Artemether and 120 mg of Lumefantrine. |
| Criteria for efficacy evaluation | Primary efficacy endpoint:  The primary efficacy endpoint will be the PCR-corrected adequate clinical and parasitological response (ACPR) at D28.  Secondary efficacy endpoints:  The secondary efficacy endpoints will be:   - Crude or PCR uncorrected adequate clinical and parasitological response (PCR uncorrected ACPR)   The comparison of the uncorrected Day 28 cure rates for both drugs will be performed.   - Fever clearance time (FCT)   Fever clearance time will be defined as the time (in hours) from the start of a patient’s treatment to the first consecutive axillary temperature measurements below 37.5°C.   - Asexual parasite clearance time (PCT)   Asexual parasite clearance time will be defined as the time (in days) from the start of a patient’s treatment to 2 consecutive negative blood slides (collected at different days).   - Gametocyte prevalence will be compared on days 7, 14, 28 and 42. - haemoglobin (Hb) will be measured at day 0, 3 , 28 and 42. - Cure rates at D42 (PCR corrected and PCR uncorrected) |
| Criteria for safety evaluation | Adverse events, laboratory parameters, vital signs, ECG. |
| Statistical Methodology | The primary analysis will be based on a 97.5% (one-sided) Confidence Interval (CI) computed on the difference between the 28-day PCR corrected cure rates of the test and the reference treatments, respectively.  In order to claim that DHA+PPQ is efficacious, the lower limit of the CI must be > -0.05 and the point estimate for the 28-day PCR corrected cure rate of DHA+PPQ must be > 0.90, in both the modified ITT and the Per Protocol populations. |
| First patient in | July, 2005 (expected date) |

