## Primary Endpoint

The primary endpoint will be the PCR-corrected adequate clinical and parasitological response (PCR corrected ACPR) at D28.

ACPR is defined as the absence of parasitaemia on D28 irrespective of the axillary temperature without previously meeting any of the criteria of early treatment failure or late clinical or parasitological failure.

Patients with late asexual parasite reappearance will be considered ACPR if the PCR analysis shows a new infection rather than a recrudescence.

The total treatment failure is defined according to the WHO criteria (WHO 2003) as the sum of early* and late** treatment failures.

* Early Treatment Failure (ETF)

*(i) Development of danger signs or severe malaria on Day 0, Day 1, Day 2 or Day 3, in the presence of parasitaemia,*

*(ii) Parasite density on Day 2 > Day 0 count irrespective of axillary temperature,*

*(iii) Presence of parasitaemia on Day 3 with fever (axillary temperature ≥ 37.5°C),*

*(iv) Parasitaemia on Day 3 ≥ 25 % of count on Day 0.*

** Late treatment failure (LTF)

Late Clinical Failure (LCF)*:*

*(i) Development of danger signs or severe malaria after Day 3 in the presence of parasitaemia, (See Appendix V for the critera for severe malaria/danger signs)*

*(ii) Presence of parasitaemia and fever on any day from Day 4 to Day 28, without previously meeting the criteria of ETF.*

Late Parasitological Failure (LPF)*:*

*Reappearance of parasitaemia after initial clearance between day 4 and day 28 (identified as recrudescent infection by PCR analysis) in the absence of fever (axillary temperature <37.5°C) without previously meeting the criteria of ETF or LCF.*

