4. PCR

A blood sample will be collected on filter paper (Whatmann 3MM) at Day 0 before treatment and every time a blood slide is done starting at and including D 14. Samples from patients classified as late treatment failure will be subsequently used for parasite genotyping.

5. Blood Slide

A thick and thin blood smear will be obtained from the subject to verify the presence of *P. falciparum* and to calculate the parasite density. Thick and thin blood films will be prepared, dried and stained with Giemsa stain according to standard operating procedures.

Parasite density will be calculated by counting the number of asexual parasites per 200 leukocytes in the thick blood film, based on a assumed WBC of 8,000 /µl by light microscopy at 1000xmagnification. One hundred high-powered fields (HPF) will be examined (independent of presence or absence of asexual parasite stages). The parasite density per microlitre will be calculated using the following formula:

Parasite density / µl = Number of parasites counted x 8,000

Number of leukocytes counted

6. Laboratory Tests

Blood haemoglobin, red blood cell count, total white blood cell count, differential count (neutrophils, basophils, eosinophils, monocytes, lymphocytes) and platelet count.

Total bilirubin, ALAT and creatinine will be measured.

7. Electrocardiogram (ECG)

A 12 lead ECG will be performed and QT/QTc interval prolongation will be evaluated. **Any patient found to have an abnormal ECG throughout the course of the study will be treated in accordance with local practice and national guidelines.**

8. Administration of the Study Drugs

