## Population Analysed

The following populations will be considered for the statistical analysis of efficacy.

**Intention-to-Treat (ITT) Population**. Defined as all randomized patients who will take at least one dose of the study treatment. All patients who withdrew from the study for one of the reasons listed in section 5 as well as the patients for whom the PCR is not interpretable or missing will be evaluated as failures. For the robustness analyses, these patients will be evaluated in different ways in this population (see section 9.2).

**Modified Intention-to-Treat (modified ITT) Population**. Defined as the ITT population with the exclusion of the lost-to-follow-up patients before Day 28 for unknown reasons (non informative drop-outs). More specifically, patients withdrawing from the study for reason 7 (see section 5) will be excluded, while all other withdrawals will be counted as failures (these reasons might be potentially considered correlated with lack of efficacy, i.e. are referred to as informative drop-outs). The patients for whom the PCR is not interpretable or missing will be assigned the result “recrudescence” or “re-infection” according to the ratio between these outcomes which was observed among the evaluable PCRs within each treatment group. This rule about PCR will be applied for the primary analysis. For all analyses for which the knowledge of the outcome is needed for each patient individually (for example, the Breslow Day test or the logistic regression or the analyses where a baseline covariate is needed), different scenarios will be considered, i.e. the most two extreme ones of considering all patients with not interpretable or missing PCRs as failures or as successes and the intermediate one of excluding them all.

**Per-Protocol (PP) Population**: defined as all randomized patients who will be eligible according to the study protocol, will receive at least 80% of the study medication, will have the Day 28 assessment, will not take other anti-malarial drugs and, in case of the presence of asexual parasite stages on thick or thin blood smears, will have an evaluable PCR. The protocol violations listed below will also be considered reasons for excluding the patients from this population:

 failure to attend a follow-up visit on Days 0-2 and patient cannot be located within 6 hours of scheduled time;

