**Day 3.**

Evaluate patient and complete Case Report Form. Collect thick blood smear and filter paper sample

**Day 7, 14, 21**. Evaluate patient and complete Case Report Form. Collect thick blood smear and filter paper sample

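### Read as written, the per-protocol criteria drop early treatment failures from a co-primary population, and the modified ITT rules leave their scoring unclear

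*Combined protocol and SAP*

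**What the plan says.** **Endpoint.** The Synopsis and section 2.1 define the cure rate as adequate clinical and parasitological "response at Day 28 plus those treatment failures identified as new infection by PCR", with no limit to late failures. Section 3.2 defines total failure as early plus late failure. It requires a child to reach Day 28 "without previously meeting any of the criteria of early treatment failure or late clinical or parasitological failure", and it confines the PCR correction: "Patients with late asexual parasite reappearance will be considered ACPR if the PCR analysis shows a new infection rather than a recrudescence".

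**Genotyping.** Section 3.8 (Visit 1, PCR) says: "Samples from patients classified as late treatment failure will be subsequently used for parasite genotyping". It takes filter paper "at Day 0 before treatment and every time a blood slide is done starting at and including D 14", and the flow chart in 3.6 marks no PCR sample on Days 1 to 3. Appendix VIII, for Day 3, says "Collect thick blood smear and filter paper sample", and asks for the same on Day 2.

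**What happens to an early failure.** Section 5 lists treatment failure, expressly including early failure, as its first reason for stopping treatment or ending efficacy assessment. Section 4.4 provides rescue treatment for ETF and late clinical failure, and for asymptomatic recurrence.

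**Populations (9.1).** The PP set requires the Day 28 assessment, no other antimalarial and, "in case of the presence of asexual parasite stages on thick or thin blood smears, will have an evaluable PCR". The modified ITT counts every withdrawal except loss to follow-up as a failure. It then adds: "The patients for whom the PCR is not interpretable or missing will be assigned the result" of recrudescence or re-infection in the ratio observed among the arm's evaluable PCRs. Section 9.2.1 requires non-inferiority in both sets.

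**The concern.** ETF is non-response within three days, and it needs no genotyping to interpret. A population meant to show the drug's effect under good adherence should keep it. Under the PP criteria as written, a child who fails early, is not genotyped and is rescued leaves the denominator instead of counting against the drug. That raises the PP cure rate in each arm. If early failures are more common on DHA+PPQ, it also moves the PP difference towards non-inferiority.

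The absolute rate matters too. The Synopsis requires a DHA+PPQ cure rate above 90% in both populations, and section 9.2.2 judges PP failure rates against the same threshold.

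The modified ITT is less exposed, but two of its rules can reach the same child and nothing says which prevails.

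**Working it through.** **1. Following one ETF through the rules**

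- *PP, PCR criterion:* parasites were seen, and 3.8 does not name early failures for genotyping, so there is no evaluable PCR. Excluded.
- *PP, Day 28 and other-antimalarial criteria:* the child is withdrawn from efficacy assessment and given rescue treatment. Excluded again, whatever the PCR status.
- *Modified ITT, withdrawal rule:* treatment failure is a withdrawal reason other than loss to follow-up. Failure.
- *Modified ITT, missing-PCR rule:* if an ungenotyped ETF counts as a missing PCR, it is split by the observed ratio. No precedence is stated.
- *Pure ITT:* failure under either rule.

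Section 5 numbers two items 6. The reason that 9.1 calls number 7 is read here as loss to follow-up.

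**2. The plan's own power figures**

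Inputs from 3.4.1: margin 0.05, one-sided alpha 0.025, 1000 + 500 randomised, attrition 10% (900/450) and 30% (700/350), cure 91% and 93%. With unpooled SE and continuity correction cc = 0.5(1/nT + 1/nC), power = Φ[(0.05 − cc − 1.96·SE)/SE].

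- Modified ITT: SE = √(0.0819/900 + 0.0819/450) = 0.01652; cc = 0.00167; power 83.3% (plan: about 83%).
- PP: SE = √(0.0651/700 + 0.0651/350) = 0.01670; cc = 0.00214; power 81.7% (plan: 82%).

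Both reproduce. No stated figure is wrong on this point.

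**3. Effect of dropping ETFs from PP**

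The documents give no ETF rate, so e is an assumption. If c is the cure rate with ETFs kept, the rate after dropping them is c/(1 − e).

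- *One arm, c = 93%:* e from 0.5% to 3% raises the rate by 0.47 to 2.88 points. At e = 2%, a rate of 89% becomes 0.89/0.98 = 90.8%, which crosses the 90% threshold.
- *Difference, true cure 86% versus 91% (on the margin), ETF 2% versus 0.5%:* 0.86/0.98 = 0.8776 and 0.91/0.995 = 0.9146. The difference is −0.0370 instead of −0.0500, a shift of **+1.30 points**.
- *Coartem at 0.5%, DHA+PPQ at 1% or 3%:* +0.41 or +2.20 points.
- *Equal ETF of 2%:* 0.8776 − 0.9286 = −0.0510, a shift of −0.10 points.
- *Excess on Coartem instead (0.5% versus 2%):* 0.8643 − 0.9286 = −0.0642, a shift of −1.42 points.

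For the 2% versus 0.5% case at 700/350, the chance of passing in PP alone goes from 1.9% (SE 0.02015, z = −2.066) to 8.0% (SE 0.01941, z = −1.402).

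**4. Modified ITT, only if the ratio rule prevailed**

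An arm's cure rate would rise by e × r, where r is the re-infection share (also an assumption). For ETF 2% versus 0.5% and r = 70%, the shift is 0.0140 − 0.0035 = +1.05 points, and the pass rate in this set alone goes from 2.0% to 7.4%. With equal e and r the shift is zero. If the withdrawal rule prevails, the shift is zero in every case.

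**The case against.** A reader might infer that the plan scores early failures as cures in the modified ITT. The documents do not support that.

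- The Synopsis credits only failures that PCR identifies as new infection, so an ungenotyped ETF gains nothing from it.
- Section 3.2 bars a child who met an ETF criterion from the favourable outcome and corrects late reappearance only.
- Sections 5 and 9.1 together count early-failure withdrawals as failures.
- A PCR can fairly be called missing only where one was due.

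This stands. What remains is narrower. Late recurrences are also treatment-failure withdrawals, so the PCR rules must override the withdrawal rule for them or no correction could occur. The text does not say that the override stops there.

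It is also too strong to say that early failures are never genotyped. That is the plain reading of 3.8, but Appendix VIII collects filter paper on Days 2 and 3.

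On PP, it can be said that the literal reading is unintended. The evaluable-PCR clause presupposes that recurrences stay in, and the planned 93% cure rate presupposes 7% failures. That is a fair inference for genotyped late recurrences. It does not help ETFs, because the PCR clause itself removes them.

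The sizes rest on unequal ETF rates that the documents give no reason to expect: both arms contain a rapidly acting artemisinin derivative. Each pass rate is for one population, whereas both must succeed, so neither is the trial's false-claim rate. The pure ITT analysis scores ETFs as failures, but only as a robustness check. Further detail is deferred to a SAP whose text is not in the documents reviewed.

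**Conclusion.** The PP defect follows from the stated rules. Three criteria in 9.1, each by itself, tend to remove early failures from a population on which the non-inferiority claim depends. Two of them, read literally, also remove late failures rescued before Day 28.

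The consequence is an overstated PP cure rate, by roughly the ETF rate itself. The difference is biased only when ETF rates differ between arms: about +1.3 points against a 5-point margin for an assumed 2% versus 0.5%, close to nothing for equal rates, and in the other direction if the excess is on Coartem. No joint error rate across the two required populations has been calculated.

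The modified ITT point is secondary: the scope of the cure definition differs between the Synopsis with 2.1 and section 3.2, and precedence in 9.1 is unstated. The sampling days in 3.8 and the flow chart conflict with Appendix VIII and must be reconciled. The plan's power is unaffected.

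**What to change.** 1. In the Synopsis and section 2.1, insert *late* before *treatment failures* in the cure definition, so that it matches 3.2.
2. In section 9.1 add: *Early treatment failures are counted as failures, without PCR, in the ITT, modified ITT and PP populations. The missing-PCR ratio rule and the evaluable-PCR criterion apply to late recurrences only. A patient who meets a failure criterion is not excluded from PP for lacking the Day 28 assessment or for taking rescue antimalarials after that failure.* The last sentence is needed: limiting the PCR criterion alone would not keep ETFs in PP.
3. Say whether the 80% dosing criterion still applies to a child whose treatment was stopped because of an early failure.
4. Reconcile the filter-paper days in 3.8, the flow chart and Appendix VIII.

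This costs a few sentences in the protocol and SAP and needs no new data. Reported cure rates may be slightly lower.

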## Sample Size

3.4.1 Sample size computation

The study is designed as a non-inferiority trial.

The level of the PCR-corrected cure rate at day 28 for Arthemeter+Lumefantrine has been estimated, through a literature search, to be in the range 90%-92%32-33 in the Intention-To-Treat (ITT) population. The opinion of physicians and experts in malaria treatment has been sought for defining the non-inferiority margin, and this has been set at 5%.

An unequal randomization with 2:1 structure was chosen because it assures a larger sample size for the DHA+PPQ group which provides the following advantages:

- a more precise estimate of the DHA+PPQ cure rate;
- a bigger sample for the integrated safety data base of DHA+PPQ, that renders more likely the elucidation of rare adverse reactions, if any.

From an ethical point of view, this choice appears reasonable in view of the previous data on DHA+PPQ, in terms of both safety and efficacy.

Sample size was initially (see original version of the protocol) computed considering the original formulation of the primary objective, which required the use of a simulation (details are provided in a separate document - see Sample Size and Design Justification for The Pivotal Clinical Trials of Dihydroartemisinin+ Piperaquine**)**.

Having divided the two criteria of non-inferiority and comparison of study results with historical ones, power has been recomputed for each of the two objectives as described below**.**

For the non-inferiority analysis, the clinical and statistical specifications for the sample size computations are as follows:

- Primary endpoint = PCR-corrected cure rate at day 28.
- Primary analysis = based on 97.5% one-sided confidence intervals for the difference in cure rates.
- Alpha = 0.025 (one-sided).
- Power = 80%.
- Cure rate of Coartem in the pure ITT population = at least 91%.
- Non-inferiority margin for the difference (test-reference) = -0.05.
- Randomization: based on a 2 :1 allocation scheme (test : reference).
- Rate of patient attrition in the modified intention-to-treat population as compared to the pure ITT population (i.e. rate of non-informative withdrawals) = 10%. Expected 28-day PCR corrected cure rate in this population = 91%.
- Rate of patient attrition in the Per Protocol Population as compared to the ITT population (i.e. rate of withdrawals for any reason and protocol violations) = 30%. Expected 28-day PCR corrected cure rate in this population = 93%.

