## Efficacy

9.2.1 Analysis for showing non-inferiority of Artekin vs Coartem

The primary analysis will be based on a 97.5% (one-sided) Confidence Interval (CI) computed on the difference between the 28-day PCR corrected cure rates of the test and the reference treatments, respectively.

In order to claim that Artekin is non-inferior to Coartem the lower limit of the CI must be > -0.05 in both the modified ITT and the Per Protocol populations. The analysis on the more pure ITT population (see section 9.1) will be used for investigating robustness of results (see below).

The method for computing the CI will be specified in the SAP.

For computing the PCR-corrected cure rate, the patients who are diagnosed to be re-infected will be counted as successes (they have to be terminated on that day of follow-up) while the patients for whom the PCR is not interpretable or the sample is unavailable will be treated differently depending on the population considered (see section 9.1).

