9.2.2 Historical comparisons

In order to compare the study results with the historical ones, the criteria described in the WHO document (“Assessment and Monitoring of Antimalarial Drug Efficacy for the Treatment of Uncomplicated Falciparum Malaria – 2003”. See chapter 7, section 7.3) will be used. Therefore, the failure rates will be estimated through survival analysis (Kaplan-Meier method) in each treatment group individually considered. This analysis will be carried-out in the per-protocol population and the results obtained in each of the two treatment groups will be judged against the threshold of 90% (there is consensus among the malaria experts in recognising that the threshold of 90% should be considered as a “rule of thumb” for judging efficacy)..

Robust analysis will be performed on the more pure ITT population by applying the following methods:

1. All patients who withdrew from the study for one of the reasons listed above (from 1 to **7**) will be evaluated as failures.

2. Patients who withdrew from the study for reasons that cannot be considered uncorrelated with the study treatments (i.e. reasons from 1 to **6**) will be counted as failures (i.e. assigned with a 0 value), while the patients prematurely interrupting the study for reason **7** will be assigned with a value ranging from 0.5 to 0.9 (imputation of a postulated probability of success for the patients for whom the treatment outcome could not be evaluated). Finally, all cured patients will be assigned with a 1 and this transformed endpoint will be summarized in terms of means and corresponding standard errors by treatment group.

3. The analysis of the 28-day PCR corrected cure rates will be performed by means of the survival analysis techniques, where the non informative lost-to-follow-up patients (i.e. patients withdrawing for unknown reasons) will be censored at the time of exiting the study.

The impact of these strategies on the conclusions will be carefully evaluated and discussed

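### The synopsis and section 9.2 state different success rules: the synopsis adds a 0.90 point-estimate condition that section 9.2.1 omits and the stated power does not cover

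*Combined protocol and SAP*

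**What the plan says.** Four places in the protocol bear on the success rule.

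- **Synopsis, Statistical Methodology.** Directly after defining the primary analysis as a one-sided 97.5% interval for the difference in cure rates, it sets the conditions for calling DHA+PPQ efficacious. The lower limit must exceed -0.05 and the "point estimate for the 28-day PCR corrected cure rate of DHA+PPQ must be > 0.90, in both the modified ITT" and PP populations. That makes four conditions: two criteria in each of two populations.
- **Section 9.2.1.** To "claim that Artekin is non-inferior to Coartem the lower limit of the CI must be > -0.05 in both" the modified ITT and PP populations. There is no point-estimate condition.
- **Section 9.2.2.** The 90% figure appears here as a historical comparison. Rates are estimated by Kaplan-Meier in the PP population, and the "results obtained in each of the two treatment groups will be judged against the threshold of 90"%. The section describes this threshold as a rule of thumb.
- **Section 3.4.1.** "Having divided the two criteria of non-inferiority and comparison of study results with historical ones", power was recomputed for each objective. It gives about 83% (modified ITT) and 82% (PP) for non-inferiority. For the 90% criterion it gives only a precision requirement of at least 200 patients per group.

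The Objectives row of the synopsis and section 2.1 both name non-inferiority as what is to be demonstrated and mention the WHO comparison separately.

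**The concern.** The rule that decides whether the trial succeeds should be the same wherever it is stated. Here the 90% threshold differs between the synopsis and section 9.2.2 in four respects: its role (part of the claim, or a separate judgement), the estimator (observed proportion, or Kaplan-Meier), the population (modified ITT and PP, or PP only) and the arms (DHA+PPQ only, or each arm).

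The modified ITT condition matters most, because the planned cure rate there, 91%, is only one point above the threshold. Suppose 808 of 900 DHA+PPQ patients (89.8%) and 405 of 450 Coartem patients (90.0%) are cured in modified ITT, and PP passes. The difference is -0.0022, its unpooled standard error is 0.0174, and the lower bound is -0.036, or -0.038 with a continuity correction. Section 9.2.1 is met and the synopsis rule is not. In an open-label trial, the choice between the two should not be left until results are known.

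**Working it through.** **Inputs (section 3.4.1).** "Alpha = 0.025 (one-sided"); "Non-inferiority margin for the difference (test-reference) = -0.05"; randomisation "based on a 2 :1 allocation scheme (test : reference"); 1000/500 patients. Attrition of 10% gives 900/450 in modified ITT with a cure rate of 91%. Attrition of 30% gives 700/350 in PP with a cure rate of 93%. The same rate is taken in both arms.

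**Step 1: reproduce the stated power.** Power = Φ[(0.05 − c)/SE − 1.96], where SE = √[p(1−p)(1/n_T + 1/n_R)] and c = ½(1/n_T + 1/n_R).

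- Modified ITT: SE = √(0.0819 × 0.003333) = 0.01652; c = 0.00167; power = Φ(0.965) = 83.3%.
- PP: SE = √(0.0651 × 0.004286) = 0.01670; c = 0.00214; power = Φ(0.905) = 81.7%.

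These match the stated 83% and 82%. Each is for non-inferiority in one population, without the 0.90 condition.

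**Step 2: the 0.90 condition alone.** With 900 DHA+PPQ patients at 91%, the exact binomial probability of 810 or fewer cures (estimate ≤ 0.90) is 0.161. In PP (700 at 93%) the estimate exceeds 0.90 in 99.8% of trials. Nearly all the effect comes from modified ITT, a population that section 9.2.2 does not use.

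**Step 3: both rules jointly.** PP is simulated as nested in modified ITT, as the section 9.1 definitions imply. The cure rate in modified ITT patients outside PP is then (900×0.91 − 700×0.93)/200 = 168/200 = 0.84. Section 9.2.1 leaves the interval method to the SAP, so four methods were run, with 1,000,000 simulated trials at the planned rates.

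| Interval | Section 9.2.1 rule (both populations) | Synopsis rule | Passes 9.2.1, fails synopsis |
|---|---|---|---|
| Wald, continuity-corrected | 78.2% | 71.6% | 6.6% |
| Wald | 81.7% | 74.2% | 7.5% |
| Farrington-Manning, corrected | 80.5% | 73.3% | 7.2% |
| Farrington-Manning | 83.7% | 75.6% | 8.1% |

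The last column is a plain subtraction, because any trial that meets the synopsis rule also meets section 9.2.1. A four-variate normal approximation with fixed standard errors runs lower (synopsis rule 69.6% corrected, 72.4% uncorrected).

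**Step 4: other true rates.** 400,000 trials each, same sizes, ranges over the four methods.

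| Modified ITT / PP | Section 9.2.1 | Synopsis | Disagree |
|---|---|---|---|
| 90% / 92% | 72.6–78.9% | 43.6–45.4% | 29–34% |
| 91.5% / 93.5% | 81.2–86.3% | 79.2–83.7% | 2.0–2.6% |
| 92% / 94% | 84.0–88.6% | 83.7–88.1% | 0.4–0.5% |

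**Step 5: population size.** The synopsis places all 1500 patients in modified ITT. With 1000/500 there at the planned rates, the synopsis rule passes in 73.2–77.1% of trials if PP stays at 700/350. It passes in 75.9–79.1% if PP scales up to 778/389.

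**The case against.** The best case for the plan is that the intention is clear. Section 3.4.1 records the split, section 2.1 and the synopsis Objectives row carry the divided version, and section 9.2.2 calls 90% a rule of thumb. On that reading one synopsis sentence escaped editing. The wording also differs: the synopsis speaks of being efficacious, section 9.2.1 of being non-inferior. The SAP is due within the first month of the study and could settle the rule early.

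The point about intention stands and determines the fix. It does not remove the conflict. The synopsis is current text, nothing in the document says which rule governs, and its sentence follows directly on the definition of the primary analysis. If efficacious is meant as a separate claim, section 9 neither defines nor powers it. The protocol does not say that the SAP will resolve the matter.

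A reader might infer something stronger: that the trial is underpowered, at 72–76% against a specified 80%. The documents do not support this.

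- The 83% and 82% are for non-inferiority in each population taken alone, and the 80% target belongs to that same non-inferiority calculation. The 72–76% is for four conditions together.
- Part of the gap comes from requiring success in both populations, which section 9.2.1 also does (78–84%, depending on the interval).
- The loss almost vanishes at 92%/94%. Section 3.4.1 cites 90–92% for Coartem in ITT, so the low end should not be shown alone.
- Section 3.4.2 plans a re-assessment that can only increase the sample size.

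Nor do the documents show any intention to choose a rule after the results. They merely leave that possible.

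**Conclusion.** The discrepancy is real and concerns the main success criterion. The synopsis rule is stricter than section 9.2.1, uses the 90% threshold differently from section 9.2.2, and is not the rule for which power is stated. The two rules disagree in about 7–8% of trials at the planned rates, about 30% at 90%/92%, and under 1% at 92%/94%. At the planned rates the 0.90 condition itself costs about 7–8 points of power. Any further distance from the stated 83% and 82% reflects the two-population requirement and the interval method.

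The textual conflict rests on no assumption, and the 16% figure needs only the planned rate and size. The joint figures assume equal rates in the two arms, PP nested in modified ITT, binomial outcomes (ignoring the proportional assignment of unevaluable PCR results in section 9.1) and one of the four interval methods. This is a fault in the statement of the success rule, not evidence that 1500 patients are too few for the analysis in section 9.2.1.

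**What to change.** Replace the claim sentence under Statistical Methodology in the synopsis with the section 9.2.1 rule: a lower bound above -0.05 in both modified ITT and PP. Then list the 90% comparison as the separate section 9.2.2 analysis (Kaplan-Meier, each arm, PP), stated not to be part of the non-inferiority claim. This costs one paragraph, no patients and no change to the stated power.

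Only if the sponsor wants 0.90 in the claim, write it into section 9.2.1 with one estimator and one population, align the synopsis and section 9.2.2 with it, and state the joint power. For the synopsis version of the condition at the planned rates, that is about 72–76% with 900/450 in modified ITT, or 73–79% with 1000/500, to be narrowed once the SAP fixes the interval method. The cost is a sentence in section 9.2.1, matching edits elsewhere and a less favourable power figure.
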